#### Primary outcome measure

The primary outcome measure is the Questionnaire about the Process of Recovery (QPR [34]), a 22-item consumer-rated questionnaire used to assess experience of personal recovery. The QPR comprises of two subscales: Intrapersonal recovery processes (17 items) and Interpersonal recovery processes (5 items), with each item being rated on a 5-point Likert scale ranging from 0 (disagree strongly) to 4 (agree strongly). A higher score indicates increased recovery [34]. The QPR subscales have good internal consistency (Intrapersonal: *r* = 0.94; Interpersonal: *r* = 0.77), test-re-test reliability (Intrapersonal: *r* = 0.874, *p* = 0.001; Interpersonal: *r* = 0.769, *p* = 0.001), and construct validity [34].

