### Sample size

The primary analysis examines QPR data from consumers in the cRCT (stream 1) and requires a total sample size of 756 consumers from 14 clusters over 3 years (see Table 1). This will be sufficient to detect a medium effect size representing a change in QPR score by 6.34, see Table 1. Secondary analyses that examine data from a subset of stream 1 consumers who participate in stream 2 of the cRCT, requires a total sample size of 252 consumers over the study period. This will be sufficient to detect medium effect sizes in the QPR and two secondary outcome measures (WEMWBS and INSPIRE), see Table 1. Additional secondary analyses to examine longitudinal data from a subset of stream 2 consumers who participate in stream 3 of the cRCT, requires a total sample size of 88 consumers over the study period. This will be sufficient to detect medium-large effect sizes in the QPR and WEMWBS and INSPIRE, see Table 1.

Sample size calculations were based on 14 clusters; intracluster correlation coefficient (ICC) of 0.05; significance level set at 0.05; power of 0.80; and available published [34, 36, 45] and unpublished (INSPIRE) data about distribution properties. All sample size calculations indicate the minimum number of participants we aim to recruit and were done using Stata statistical software *stepped-wedge* [46] Version 11, StataCorp. 2009.

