The analysis of data in a stepped-wedge cRCT is most suitably analysed in mixed-effects models [54]. The primary analysis examines the effect of PULSAR on the primary outcome (consumer-level QPR scores) using a linear mixed-effects model state ‘on an intention-to-treat basis’. The model will include intervention status and time as fixed effects and clusters and consumers as random effects. Normally step one is just to examine intervention – control group differences controlling for cluster, before including covariates. An a priori model-fitting analysis strategy will involve both univariate and multivariable models to be developed based on baseline consumer and cluster-level variables considered statistically significant (*p* < 0.10) or clinically important (e.g., age, sex), see Table 5, and included in the model as fixed. Model fit will be examined by comparing AIC values.

Secondary analyses will examine the effect of PULSAR on secondary outcomes (WEMWBS and INSPIRE) using a linear mixed-effects models to compare the intervention and control periods (pre-intervention).

Estimated intervention effects will be reported as the mean outcome difference for continuous outcomes and Odds Ratio for binary outcomes between intervention and control periods. This can be described as a meta-analysis approach as (in the case of continuous data) the mean change in each cluster will be standardized by using the variance of the outcome measure within that cluster. The estimated intervention effects will be reported with 95% Confidence Intervals and *p* values. Analysis will be conducted using Stata V.14, StataCorp. Stata Statistical Software: Release 14. College Station, TX: StataCorp LP, 2015.

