#### Sensitivity analyses

A missing data analysis will investigate any patterns of missingness. For each primary and secondary outcome component with missing data, multiple imputation using multivariate regression with factors of age, gender, time, and intervention status will produce 100 estimates. Sensitivity analyses will be performed using this multiple imputation to account for missing data and then re-running the analyses. Sensitivity analyses will also include the intervention dosage variable described earlier.

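### The imputation model names four factors and leaves out the respondent's answered items, stream 1 QPR and cluster, so its value as a sensitivity check depends on an undefined imputation unit

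*Protocol article*

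**What the plan says.** The Sensitivity analyses section opens with a review of missingness: "A missing data analysis will investigate any patterns of missingness". It then fixes an imputation procedure. The unit is set by "For each primary and secondary outcome component with missing data" and the method by "multiple imputation using multivariate regression with factors of age, gender, time, and intervention status will produce 100 estimates". Its role is that of a check on the main result: "Sensitivity analyses will be performed using this multiple imputation to account for missing data and then re-running the analyses".

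The section does not say whether a component is an item, a subscale or a total score. The QPR is "a 22-item consumer-rated questionnaire used to assess experience of personal recovery", with subscales of 17 and 5 items (Primary outcome measure), so all three readings are possible.

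The analysis model is in the Main analysis plan for cRCT: "The model will include intervention status and time as fixed effects and clusters and consumers as random effects". Further covariates enter later models if "considered statistically significant (*p* < 0.10) or clinically important (e.g., age, sex").

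**The concern.** Time and intervention status are already fixed effects in the primary model. Age and sex are the examples given of clinically important covariates. An imputation built on these four factors draws on almost nothing that the adjusted analysis lacks.

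More informative data will be to hand. For an incomplete QPR, these are the other answers on the same form. For WEMWBS and INSPIRE, they include the person's QPR, because stream 2 is a subset of stream 1 (Table 1; cRCT data collection). Cluster is not named either, although the analysis model has a cluster random effect.

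This is the only analysis described that is meant to account for missing outcomes. If people who score low skip items more often in one condition, one permitted version of it would agree with the main result while both carried the same bias, and the result would be reported as robust.

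**Working it through.** **1. The plan's own figure, for scale.** Inputs from Sample size and Table 1: 14 clusters, 3 periods, 18 per cluster-period (756 / 14 / 3), ICC 0.05, alpha 0.05 (two-sided assumed), power 0.80, and seven clusters crossing at each step. The Hussey–Hughes variance, in units of SD², is

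Var = I·s²·(s² + T·t²) / [(I·U − W)·s² + (U² + I·T·U − T·W − I·V)·t²]

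with I = 14, T = 3, s² = 0.95/18 = 0.0528, t² = 0.05, U = 21, W = 245, V = 35. The numerator is 14 × 0.0528 × 0.2028 = 0.1498. The denominator is 49 × 0.0528 + 98 × 0.05 = 7.486. Var is therefore 0.0200 and the SE 0.1415. The detectable difference is (1.960 + 0.842) × 0.1415 = 0.396 SD. The article says "This will be sufficient to detect a medium effect size representing a change in QPR score by 6.34", which implies an SD of 6.34 / 0.396 = 16.0. No SD is stated, so 6.34 can be neither confirmed nor refuted. It serves here only as a yardstick.

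**2. What each reading does with a partly blank form.** Let B be the bias when incomplete forms are dropped and skipping depends on the score.

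- *Whole score imputed from the four factors:* the answered items are discarded. The imputed totals follow the regression fitted to complete forms, so the bias stays at about B.
- *Items imputed separately from the four factors:* the answered items stay in the total and only k of 22 items are redrawn. With similar items, about (k/22)·B remains: 1/22 = 5%, 2/22 = 9%, 8/22 = 36%.
- *Items imputed jointly, using the answered items:* little bias remains, because the answered items carry the score.

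**3. Simulation, score-related skipping, true effect 0.** Assumed: the design above, SD 16, alpha 0.94 for the total (the article gives 0.94 only for the 17-item subscale and 0.77 for the other), and about 12% of forms incomplete, skipped more often by low scorers in trained clusters. There were 150 trials, with a Monte Carlo SE of about 0.19 and all methods on the same data sets.

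| Analysis | 2 blanks | 8 blanks |
|---|---|---|
| Full data | 0.13 | 0.24 |
| Complete forms | 2.39 | 2.62 |
| Complete forms, age/sex-adjusted | 2.38 | 2.61 |
| Four factors, whole score | 2.43 | 2.65 |
| Four factors, by item | 0.32 | 1.05 |
| Using answered items | 0.14 | 0.25 |

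Net of the full-data value, item-level four-factor imputation leaves (0.32 − 0.13) / (2.39 − 0.13) = 8% of the bias with two blanks and (1.05 − 0.24) / (2.62 − 0.24) = 34% with eight. Both agree with step 2.

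**4. Second simulation, true effect 6.34.** Assumed: inter-item correlation about 0.45, SD about 15, and the last 8 items skipped by 16% of people, depending on the 14 answered items in opposite directions by intervention status. There were 300 trials, with a Monte Carlo SE of about 0.13. Bias was +0.17 with all data, +4.27 with complete forms, +1.57 with four factors by item, and +0.18 with joint imputation. The +1.57 is 1.57 / 6.34 = 25% of the plan's detectable difference.

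**5. Where the four factors suffice.** If a whole outcome is missing depending on age and intervention status, bias is +1.17 for complete cases without age, +0.07 for complete cases adjusted for age, +0.07 for four-factor imputation and +0.07 with all data. If 8 items are blank for the same reason (22% of people), it is +1.11 for complete forms, +0.05 for four factors by item and +0.06 for joint imputation.

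**The case against.** The strongest reply is that the plan may already do the right thing. A multivariate regression has several outcomes on its left side. If the components are the items and are imputed together, the answered ones inform the missing ones. The text neither says that the four factors are the only predictors nor excludes answered items. This stands as a possible reading. It is not the stated one, and a separate regression for each component fits the sentence at least as well.

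A reader might infer that the imputation recovers nothing. The article does not support that. If items are imputed, answered items stay in the total even under the four-factor model. With about 11% incomplete forms and a complete-form bias of 1.6 points, imputing items from intervention status alone left 0.06–0.07 with one blank and 0.13–0.15 with two, so over 90% of the bias was removed.

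A reader might also infer that the check cannot disagree with the main result. That fails too: age and sex are not in the first model, and step 5 shows four-factor imputation correcting an unadjusted estimate.

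Finally, an article may leave full predictor lists and item-scoring rules to an analysis plan that is not shown. That is fair for detail left out. Here, however, the article does commit to a named factor list and a number of imputations, and that list can be improved with data the trial already plans to collect.

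**Conclusion.** The point holds in conditional form. The stated factor list is thin and the imputation unit is undefined.

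- **Whole score or subscale imputed:** the sensitivity analysis adds essentially nothing beyond the age- and sex-adjusted observed-data analysis and reproduces bias from score-related skipping (2.43 against 2.38 with two blanks).
- **Items imputed from the four factors:** about nine-tenths of the bias goes when one or two items are blank, but about a third remains when eight are.
- **Answered items used jointly:** the result was at least as good, within simulation error, in every scenario that compared it with the four factors, and clearly better when many items were skipped in relation to the score.

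The sizes rest on assumed rates, mechanisms, SD and item correlation, because the article gives no missing-data rate or mechanism; only the ordering should be relied on. It cannot be claimed that the trial's result will be biased. The consequence is limited to a sensitivity analysis, and no version of it addresses people who never return the survey.

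**What to change.** In the Sensitivity analyses section:

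1. Define *component* as the questionnaire item, and impute all items of a scale jointly with age, gender, time and intervention status, so that answered items inform blank ones.
2. Include cluster in the imputation model, to match the random effect in the analysis model.
3. Add the person's stream 1 QPR as a predictor for WEMWBS and INSPIRE.
4. State that INSPIRE ratings absent by design (Support items not rated important or for which support is not wanted, and stream 3 participants with no service contact in the previous 12 months) are not treated as missing.

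A delta-adjusted run for wholly missing outcomes would be a reasonable addition, but it is optional.

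The cost is a few sentences and a larger imputation model, which may be harder to fit for the interview outcomes (252 / 14 = 18 planned interviews per cluster). No new data are needed, provided that each interviewee's survey can be linked to the interview.

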#### Economic evaluation

Overall, costs associated with each participant will follow well established health economic principles [53], and cover direct medical costs of illness, plus the labour market effects of illness. Direct medical costs are to be calculated for prescription and other medically recommended non-prescription medications, and hospital and health service contacts. Labour market productivity losses will be imputed using the human capital approach by multiplying reported days off work due to mental illness with an individual’s estimated salary using instrumentation devised by this team for a previous health economic evaluation [54]. Using only days off work due to illness to capture labour market costs captures an important aspect of the cost of illness; however, it is noted that the estimates obtained will be conservative and the true cost will be higher than what we obtain because of other effects of illness such as higher rates of non-participation in employment, or underemployment.

### Leadership structure

The PULSAR project adopts a module based advisory structure, overseen by a project steering group chaired by Principal Investigator (PI), [name]. Four modules guide and monitor the implementation and evaluation of the project which are chaired by different members of the senior research team. The modules include Adaptation, Implementation, Research and Dissemination.

Based on the REFOCUS project [55, 56], and consistent with the commitment to co-design [10, 11], PULSAR is also supported by LEAP, an advisory group comprising people with either lived experience of mental illness or with experience of caring for someone with mental illness. LEAP was established at the commencement of the PULSAR project and continues to meet during the trial. It provides consumer and family/carer perspectives on the project and ongoing feedback and advice on the trial.

### Specification of safety parameters

No plans were made for a premature stopping of the trial. Apart from any possible breaches to consumer confidentiality, which are classified as moderate risk, all risks to the safety of consumer and specialist staff are classified as minimal.

### Safety oversight

Comprehensive project protocols have been developed to address staff safety, the management of participant distress, suicidal ideation or intent, threat to harm others, and disclosure of previously undisclosed criminal acts. These protocols are readily accessible to all PULSAR research and administrative staff and are reviewed and updated on a continuing basis throughout the trial.

### Dissemination policy

#### Overview

PULSAR takes a multi-tiered approach to dissemination to maximize the translation of knowledge into practice. Dissemination avenues will include: publication of a training manual and associated resources; development of online resources to disseminate project materials to interested parties locally and abroad; publication of project protocols and findings from each component of the project in peer-reviewed literature; production of a regular newsletter updating stakeholders on project progress and outcomes; presentations and national and international conferences; local distribution through partner organizations in the community mental health sector in Victoria; and direct communication of project outcomes to key policy makers.

#### Rights

In relation to copyright issues in dissemination of findings, PI [name] and CI [name] have agreed to highly accessible publication to maximize dissemination. Specifically, there is no plan to commercialize outputs of this work and so put barriers in the way of use by others. It has been the practice of the multiple research teams involved in the PULSAR proposal to actively seek to make materials widely available as far as possible without cost, and to place barriers in the way of others commercializing such work. For example, the London REFOCUS team have disseminated the REFOCUS intervention in free-to-access booklets and through open access journal articles. The dissemination plan will make the findings widely and readily available along with source training materials.

## Discussion

The PULSAR Specialist Care trial will examine the efficacy of a recovery-oriented practice training intervention for specialist mental health care staff using a two-step stepped-wedge cRCT design. This design is often favoured for such community-based pragmatic trials, as the intervention will eventually be delivered to all participating clusters but can be implemented in stages to manage the practical constraints associated with delivering a large-scale intervention across multiple sites [20, 21]. The challenges encountered in the trial are providing valuable insights on how to facilitate staff adherence to the training and hence the embedding of the intervention into participating services, as well as effective methods for engaging and retaining the participation of consumers. A significant contribution of the work will be the production and dissemination of a package of professional training resources to support the implementation of recovery-oriented practice into community-based mental health services. Although the PULSAR materials have been developed according to the needs of the Australian mental health system and the local social, legal and cultural contexts, we anticipate that these resources will be adaptable to other settings and jurisdictions. In line with the approach taken by our UK partner, the PULSAR materials will be made widely and readily available.

With the current emphasis in mental health policy on refocusing services towards recovery, the results of this trial, including an assessment of clinical, organizational and health economic outcomes, will contribute to the small but growing evidence-base promoting the development of recovery-oriented service frameworks. If successful, it will be the most definitive trial to date in Australia demonstrating that the concept of recovery, and interventions designed to foster recovery-oriented staff behaviour and relationships with consumers, can be operationalized and comprehensively evaluated. Findings, and other information gathered and lessons learned during the trial, will support the continued transformation of the mental health sector towards recovery, ultimately leading to improved outcomes for people with serious mental illness.

## Abbreviations

ANZCTR: Australian New Zealand Clinical Trials Registry
CATT: Crisis assessment and treatment team
CCT: Continuing care team
CCU: Community care unit
CI: Chief investigator
cRCT: Cluster randomized control trial
CSQ: Client satisfaction questionnaire
GAF: Global assessment of functioning scale
HoNoS: Health of the nation outcome scales
HREC: Human Research Ethics Committee
ICC: Intraclass correlation coefficient
LEAP: Lived experience advisory panel
MASS: Mind Australia Satisfaction Survey
MHCSS: Mental health community support services
MST: Mobile support and treatment team
PALS: PULSAR active learning sessions
PARC: Prevention and recovery in community
PARIHS: Promoting action of research implementation in health services
PI: Principal investigator
PICF: Participant information and consent form
PNCQ: Perceived need for care questionnaire
PULSAR: Principles unite local services assisting recovery
QPR: Questionnaire about the process of recovery
SOFAS: Social and occupational functioning assessment scale
SPIRIT: Standard protocol items: recommendations for interventional trials
WEMWBS: Warwick-Edinburgh mental well-being scale
